### Data collection

#### Patient-reported data

Participant survey data will be collected and managed using REDCap electronic data capture tools hosted at Queensland University of Technology^27 28^ at three time periods (T1 – T3). All participants (intervention and control) will have the option to be emailed a link to online surveys or sent paper-based surveys. If surveys are not completed within 2 weeks of sending, a research nurse will contact the patient to encourage them to complete it.

#### Clinical data

Information about the participant’s cancer (histology, grade and stage of disease at diagnosis), date of diagnosis and treatment (surgery, chemotherapy and radiotherapy doses and dates) is obtained from medical records at T1 and entered into the REDCap database. Information will be obtained from health service medical records relating to hospital admissions and follow-up appointments including physical breast exam, mammography and endocrine therapy adherence occurring within the first 12 months post enrolment.

#### Stakeholder interviews

When they initially consent to the trial, participants will be invited to indicate agreement to participate in an optional interview to explore their experience of the *IBIS-Survivorship* shared care model. Patients allocated to the *IBIS-Survivorship* intervention who indicated a willingness to be approached for the interview will be invited to participate between 13 months and 24 months post enrolment. Participants will be informed that if they do not wish to participate in the interview, their current and future medical care will not be affected. In total, approximately 30 participants will be selected for the qualitative interviews based on maximum variation sampling to capture a broad range of perspectives. Additionally, all health professionals who contribute to the implementation of the *IBIS-Survivorship* model (BCNs, oncology specialists and GPs) will be invited to participate in an interview after completion of the trial to describe their satisfaction with the model, as well as barriers and facilitators experienced when implementing the intervention. Health professionals will be free to opt out of the interview process, and verbal acceptance to take part in an interview will be considered implied consent.

All interviews will be conducted via telephone or videoconferencing by a researcher skilled in qualitative interview techniques using the interview guide provided in online supplemental material BC. Participants will be encouraged to speak openly and to describe their experience with the *IBIS-Survivorship* intervention. All interviews will be audiorecorded and transcribed verbatim for analysis. It is anticipated that interviews will take approximately 30 min per participant.

### Sample size

The sample size is fixed by the number of clusters, the study duration and funding constraints. Initially, it was expected that seven cancer centres (clusters) would participate in the study; however, one cancer centre was unable to participate due to COVID-19 impacts on the health service, thus the sample size calculation and randomisation were determined after the number of clusters was confirmed as six. It is anticipated that the total number of available patients with early breast cancer will be 1384; split across the six clusters and nine cluster periods in the design. Assuming 22% of patients cannot identify a regular GP or decline participation (based on Cancer Australia’s pilot study),^29^ the potential sample size for recruitment is 1079. We will also allow for attrition of 30% by 12 months or T3 (conservative estimation based on the PROCARE Trial),^16^ thus the expected sample size for patient-reported data collection at T3 is 755 (equivalent to an average of 13 per cluster period and 125 per cluster, although varying cluster sizes are expected).

Using the online RShiny App,^41^ we estimated the power to detect a minimum clinically important difference in primary outcome (FACT-B mean scores at 12 months) between groups, of 8 points and a SD of 19 (total score possible=148), with a 2-sided type I error rate of 0.05. There is little information to support likely values of the intracluster correlation coefficient (ICC), the cluster autocorrelation coefficient (CAC) and the coefficient of variance (CV), so values were estimated from the literature. We allowed for clustering (assuming a within-period ICC of 0.03 and CV of 0.3) and for varying cluster sizes.^35^ To explore sensitivity, ICC estimates of 0.03 (0.005–0.05)^25^ and CV estimates of 0.3 (0.1–0.5) were used. Due to the longitudinal nature of this trial, correlations may differ in the same cluster period and in different cluster periods. Adjustment for time-varying correlations is made using a discrete time decay correlation structure, and the CAC is used to adjust for the correlation between two means in the same cluster at different times. Sensitivity of the CAC was explored using scores of 0.8 (0.6–0.9) in power calculations.^26^ Under these assumptions, the power curves reveal that under most anticipated scenarios, the trial will have 90% power in some conservative but plausible scenarios.

### Randomisation and blinding

The unit of randomisation is the cluster. Using the SW-CRT design, each cluster will begin the study as a control site, providing usual care follow-up to participants as per figure 1. An independent statistician randomly generated the order of the clusters, which will be concealed from all investigators and revealed to the cluster investigators 8 weeks prior to the crossover date by the project coordinator. All other clusters will be blinded to the site randomisation. Covariate constrained randomisation was used to balance the number of cluster-periods from a metro and regional cluster across the intervention and control periods. All possible randomisation schemes (720) were simulated. The balance of the randomisation schemes was then scored using the weighted squared difference in the mean values of regional across the intervention and control cluster-periods (where the weight was the inverse variance of the cluster means). A randomisation scheme was selected from the 20% of schemes with the best balance.

During each cluster period, research nurses at each cluster will identify eligible breast cancer patients and invite them to participate in the study. The research nurse recruiting participants will be blind to the randomisation sequence. The randomisation schedule will be kept centrally and only accessible by the project coordinator. The BCNs at each cluster will be informed 8 weeks prior to the crossover date when they will implement the intervention, to allow time for training in intervention delivery. The BCNs will only deliver the intervention to participants enrolled after the cluster’s crossover date. Participants are unable to be blinded and will be informed by their BCN whether they are receiving usual care (control) or *IBIS-Survivorship* care (intervention) at their first clinical appointment following enrolment to the study.

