### Study population and study sites

The target population is adults aged 18 years or older diagnosed with early breast cancer as defined by a stage I-III diagnosis (inclusive of ductal carcinoma in situ and locally advanced breast cancer but no distant metastases); within 10 weeks of completion of adjuvant cancer treatment or surgery (if not scheduled for further adjuvant therapy) at a participating cancer centre. Participants will be eligible if they are able to identify a usual GP or GP practice, are ambulatory with an Eastern Cooperative Oncology Group performance status of 0–2 and are able to read and understand English. Cancer survivors will be excluded if they have metastatic breast cancer or the presence of severe mental, cognitive or physical conditions that would limit their ability to participate (as determined by their treating clinicians). Recurrent or secondary primary breast cancer, comorbidities, other prior cancer diagnoses or treatment of trastuzumab (or biosimilars), neoadjuvant and/or ongoing endocrine therapies are *not* exclusion criteria.

The participating cancer centres (clusters) include the Princess Alexandra Hospital (Brisbane, Queensland), Sunshine Coast Hospital and Health Service (Sunshine Coast, Queensland), Gold Coast Hospital and Health Service (Gold Coast, Queensland), Ipswich Hospital (Ipswich, Queensland), Calvary Mater Newcastle (Newcastle, New South Wales) and Canberra Hospital (Canberra, Australian Capital Territory). These centres are large government-funded hospitals that are expected to treat ≥200 people with early breast cancer each year and currently employ at least one breast cancer specialist nurse (BCN). The study opened at all sites in May 2021 and recruitment closed in November 2023. Data collection is ongoing, expected to be finalised in November 2025.

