### Study design

The study will employ a SW-CRT design that involves the sequential rollout of the *IBIS-Survivorship* intervention to each of the clusters in a predetermined, randomly allocated order within the study period. Each sequence of treatments per cluster comprises nine cluster periods (see figure 1). In each cluster period (time of measurement), assessments are collected for each cluster and treatment received. All clusters commence in the usual care condition (standard cancer follow-up care), then every 18 weeks (cluster period) one cluster will crossover from usual care to implementation of the *IBIS-Survivorship* intervention. In each cluster, participants who are enrolled in the study prior to the crossover date will be in the usual care arm and will continue to receive usual care. There is no formal transition period, so participants will continue to be enrolled to clusters and receive usual care during the last 8 weeks of that cluster period until the crossover date. Once a cluster has crossed over to the intervention arm, participants enrolled in the study in the following cluster periods will receive the intervention. Thus, participants will not be exposed to both treatment conditions. Enrolment will stop at the end of cluster period seven when all clusters are in the intervention arm. The study intervention delivery will continue for a further two cluster periods (36 weeks) and will formally end when outcome data are collected from the last enrolled participants. The SW-CRT design allows for a staged implementation process which is helpful when simultaneous rollout of an intervention to all clusters is impractical due to logistical and financial constraints.^26^

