### Participant screening and consent

Research nurses will carry out initial screening to identify potential participants. Potential participants will then be reviewed according to the eligibility criteria by a member of the treating team, and if suitable, asked if they agree to be approached by a research nurse for consent to the study. These potential participants will be provided with a brochure giving detailed information about the study objectives and a Participant Information and Consent Form (PICF) providing details of the study assessments and procedures (online supplemental material B). Participants will be given up to 2 weeks to consider their participation. Participants will provide written informed consent to be enrolled into the trial. All participants will be asked to consent to allow the study team access to their medical record, and a separate written consent form will be used to indicate the participant’s willingness to allow for access to Australian Medical Benefits Schedule and Pharmaceutical Benefits Scheme (PBS) data through Services Australia.

Once a participant consents, this will be recorded in a REDcap^27 28^ database and they will be assigned a unique study ID number. Participants will be automatically invited to complete a baseline survey (T1) on enrolment. This provides sociodemographic information, medical/health history and baseline measures for patient-reported outcomes. If they do not complete this survey within 10 weeks of completion of adjuvant cancer therapies or surgery, the participant will be withdrawn from the study.

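### Arm follows enrolment date, and site staff learn the crossover date while patients can still be enrolled on either side of it; recruiter blinding to the sequence is a weak safeguard, and no stated analysis tests for selection around crossover

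*Protocol article*

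**What the plan says.** All references are to the protocol article.

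- **Arm rule.** Study design: "participants who are enrolled in the study prior to the crossover date will be in the usual care arm". Randomisation and blinding: "The BCNs will only deliver the intervention to participants enrolled after the cluster’s crossover date".
- **Who knows the date.** The cluster order is concealed and then "revealed to the cluster investigators 8 weeks prior to the crossover date by the project coordinator". The same section adds: "The BCNs at each cluster will be informed 8 weeks prior to the crossover date when they will implement the intervention". The research nurse is not named among those told, and only the project coordinator can access the schedule.
- **Enrolment during the notice period.** Study design has no formal transition period: "participants will continue to be enrolled to clusters and receive usual care during the last 8 weeks of that cluster period until the crossover date".
- **Patient window.** Study population and study sites: "within 10 weeks of completion of adjuvant cancer treatment or surgery (if not scheduled for further adjuvant therapy". Participant screening and consent allows up to 2 weeks to consider, and withdraws anyone whose baseline (T1) survey is not completed within the same 10 weeks.
- **Who decides on approach.** After the research nurse's initial screening, potential participants are "reviewed according to the eligibility criteria by a member of the treating team", who also asks whether the patient agrees to be approached. One exclusion (severe mental, cognitive or physical conditions) rests on the treating clinicians' judgement.
- **Blinding claim.** "The research nurse recruiting participants will be blind to the randomisation sequence".
- **Analysis.** The primary model adjusts for baseline FACT-B and metropolitan or regional location. Sensitivity models add patient covariates such as age, education, disease or treatment variables and comorbidities. A further analysis uses the actual crossover date where it differs from the planned one.

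**The concern.** In a stepped wedge with individual consent, randomising the cluster order protects the comparison only if the time at which a patient enters is unrelated to knowledge of the crossover date. Here the eligibility window (10 weeks) is longer than the notice (8 weeks). A patient who finishes treatment during the notice period still has at least 2 weeks of eligibility left when the site crosses over. Staff who know the date, or work beside those who do, could enrol that patient now into usual care or later into the intervention.

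If patients with greater perceived need, or greater motivation, were more often held back, the last control cell and the first intervention cell at each site would differ for reasons other than the intervention. Adjustment for baseline FACT-B, location and measured covariates removes only what those variables capture. The actual-crossover-date analysis moves the boundary but keeps enrolment date as the rule, and the per-protocol analysis excludes by receipt of the intervention. None of them tests for selection at the boundary.

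**Working it through.** **1. The plan's own figures.** 1384 × (1 − 0.22) = 1079.5 and 1079 × (1 − 0.30) = 755.3, matching the stated 1079 and 755. Enrolment runs for seven 18-week periods in six clusters, so a cell holds 755/42 = 18 participants at T3. I used generalised least squares on cluster-period means with period fixed effects, discrete-time decay, ICC 0.03, CAC 0.8, SD 19 and equal cells. The standard error is 2.45 and power for 8 points is 90.5%, consistent with the stated 90%.

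**2. Patients exposed.** Site-weeks of enrolment: 6 × 7 × 18 = 756. Rate: 1079/756 = 1.427 per site-week.

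- Finishing treatment in the 8-week notice window: 6 × 8 × 1.427 = 68.5, about 69 (6.3%); × 0.70 = 48 at T3.
- Finishing in the 10 weeks before crossover: 6 × 10 × 1.427 = 85.6, about 86 (7.9%); × 0.70 = 60 at T3. This is an upper bound.

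**3. How many could actually be deferred.** A patient who would have enrolled t weeks before crossover, after a delay D since treatment, can be deferred only if eligibility outlasts crossover, that is 10 − D > t. Assume D is uniform on 0 to 10 weeks and that deferral needs the 8-week notice.

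- Deferrable intake = ∫₀⁸ (10 − t)/10 dt = 8 − 3.2 = 4.8 weeks per site.
- Reserving 2 weeks for consent and the T1 survey: ∫₀⁸ (8 − t)/10 dt = 3.2 weeks per site.

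Across six sites these are 6 × 4.8 × 1.427 = 41 and 6 × 3.2 × 1.427 = 27 participants.

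**4. Possible shift in the estimate.** In the model of step 1, the weights on the six last-control cells sum to −0.664 and those on the six first-intervention cells to +0.664. Let w be the deferrable weeks, f the fraction of them deferred, k = f × w/18 the share of a cell that moves, and d the residual difference in 12-month FACT-B between those moved and the rest. Then

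shift = 0.664 × d × [k/(1 − k) + k/(1 + k)] = 0.664 × d × 2k/(1 − k²).

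Example: w = 10, f = 0.25 gives k = 0.139, and 0.664 × 5 × 0.278/0.981 = 0.94.

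| Deferrable weeks w | f = 25%, d = 5 | f = 50%, d = 5 |
|---|---|---|
| 10 (upper bound) | 0.94 | 2.00 |
| 8 (notice window) | 0.75 | 1.55 |
| 4.8 (uniform delay) | 0.44 | 0.90 |
| 3.2 (and 2 weeks for consent and T1) | 0.30 | 0.59 |

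The sign follows d: deferring worse-off patients works against the intervention, and deferring better-off patients favours it. The values of f and d and the uniform delay are my assumptions; the article gives none of them.

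**The case against.** A reader might infer that recruiter blinding cannot hold. The text does not support that. The claim concerns the sequence, the nurse is not among those notified, and the schedule is held centrally, so before crossover the statement can be true as written. Leakage within a site is plausible but is an inference. Open allocation after crossover is inherent in a one-way stepped wedge and contradicts no sentence in the article.

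A reader might also infer that nearly every patient finishing treatment in the 10 weeks before crossover could be steered, or that 10/18 = 56% of each last control period's intake is movable. That would require patients otherwise to enrol on the day treatment ends. A patient who finishes 10 weeks before crossover has no eligibility left after it, notice is 8 weeks rather than 10, and consent and the T1 survey must fit into what remains. With those limits the deferrable intake falls to about 3 to 5 weeks and the shift roughly halves or more.

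The planned covariate-adjusted sensitivity models also help with measured imbalance. Finally, the article gives only an overview of the analysis plan, so the absence of a particular sensitivity analysis or of screening counts by cluster-period is not in itself an error.

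These points limit the size and the wording. They leave standing the combination of date-driven arm, 8-week notice, continued enrolment, a longer eligibility window and treating-team control of approach, and none of the stated analyses deals with selection on unmeasured need or motivation.

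**Conclusion.** The concern holds in limited form. Around each of the six crossovers, arm is predictable to some site staff and open to timing for a small group of patients: about 69 of 1079 (6%), at most 86 (8%), and fewer once the T1 deadline is counted. Recruiter blinding to the sequence is a weak safeguard before crossover and none afterwards.

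On assumed deferral of 25% to 50% and an assumed 5-point residual difference, the primary estimate would shift by roughly 0.3 to 2 points in either direction. That is under one standard error (2.45) and at most a quarter of the 8-point target: not enough to overturn a clear result, but enough to matter for a borderline one. A reader might infer that allocation was in fact manipulated; the article gives no evidence of that, and the finding is about opportunity only.

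**What to change.** **Sensitivity analysis.** Before analysis, prespecify a repeat of the primary FACT-B model that excludes, in both arms, participants whose treatment-completion date falls in the 10 weeks before their site's crossover date. Anyone who finished earlier could not be enrolled after crossover, and anyone who finished later had not completed treatment before it, so the remaining participants had no choice of side. Treatment dates (Clinical data) and consent dates (Trial and data management) are already recorded. Recruitment closed in November 2023 but data collection is expected to run to November 2025, so this could still be fixed in advance.

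**Cost.** One extra model, with up to about 8% fewer participants. They come from the cells beside crossover, so precision falls somewhat more than 8% suggests. In the model used above the standard error rises from 2.45 to 2.65 if the excluded 10 weeks of intake are split evenly between the two cells (each loses 5/18), or to 2.68 if all come from the last control cell (it loses 10/18). The primary analysis is unchanged.

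**Wording.** Limit the blinding statement to the period before a site is notified of its crossover date.

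**Optional.** A second model may assign arm by treatment-completion date. It relabels as usual care some participants who properly enrolled after crossover and received the intervention, so it should be reported as diluting the effect. Screening and consent counts by cluster-period would help readers, but belong to the results report.

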### Data analysis

Provided below is an overview of the statistical analysis plan. Analyses will be conducted independently by statisticians at Queensland University of Technology, using STATA V.18.

Following data cleaning, frequencies will be generated for all variables. Scales will be created, and descriptive statistics determined according to the distribution. Differences in demographic and medical characteristics between intervention and control groups at baseline will be described using numbers and percentages, means and SD or medians and IQRs as appropriate. Every effort will be made to follow up with participants to minimise any missing data as a potential for bias. Missing data patterns will be investigated, but there will be no imputation for missing data and analyses will only be conducted on outcome variables with complete data. The following analyses will be conducted under the assumption of missing at random.

#### Analysis of effectiveness outcomes

Analyses will be conducted as intention to treat, and clusters will be considered exposed to the intervention postrandomised crossover date. This will include all eligible patients for whom data have been obtained, from enrolment to 12 months. Data will be analysed with respect to the treatment specified for each cluster by the allocated randomisation order.

The primary and secondary continuous outcomes will be analysed using a linear mixed model with an identity link function using a restricted maximum likelihood approximation with a Kenward-Roger approximation which is suitable for small samples.^42 43^ Results will be presented as mean differences between groups with 95% CIs.

The primary outcome will be assessed in a model which will include a random cluster effect, a fixed effect for period (1-9) and a random cluster by period effect to test the difference in means between groups (usual care vs intervention) for FACT-B scores at 12 months. This will estimate the time-averaged effect of the intervention. The random cluster by period interactions will allow for correlations within clusters to decay with increasing separation between times of measurement of observations. Adjustments will be made for the baseline FACT-B scores (as a covariate) and for factors used in the randomisation procedure (metropolitan vs regional location of cancer centre).

Sensitivity analyses will be conducted to estimate the effect of time since exposure, where time since exposure is a fixed effect (1-8). This will assess the effect of the intervention after one period of exposure, two periods of exposure and up to eight periods of exposure compared graphically in forest plots. Additional sensitivity analyses will adjust for patient level covariates (eg, age, education, living arrangement, disease or treatment variable and number of comorbidities) based on expert clinical guidance. The selection of baseline characteristics is based on clinical concern for imbalance between intervention groups or variables that are most prognostic of the outcome.

Similar analyses will be conducted for all secondary outcomes at 6 months and 12 months, including analysis of the difference in means between groups for FACT-B scores at 6 months. Results will be presented as mean differences between groups with 95% CIs.

A per protocol analysis will be completed for primary and secondary outcomes of the trial, which will exclude departures from randomisations such as participants randomised to receive the intervention who did not receive the intervention. These participants will be removed from the analysis. The two key components of the intervention (nurse-led consultation and GP case conference) will be considered intervention ‘doses’ and the per protocol analysis will be used to compare groups who completed either the full intervention or half the intervention with those on usual care. A further analysis will use the actual cluster cross-over date if there is variation from the proposed crossover date.

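### The random effects listed for the primary model do not, as ordinarily fitted, give the decaying within-cluster correlation claimed for them, and they differ from the structure used for power

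*Protocol article*

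**What the plan says.** Under Analysis of effectiveness outcomes, the protocol article builds the primary model for 12-month FACT-B from "a random cluster effect, a fixed effect for period (1-9) and a random cluster by period effect". It then describes what the last term does: "The random cluster by period interactions will allow for correlations within clusters to decay with increasing separation between times of measurement of observations". It names no covariance type for the cluster-by-period effects. Estimation is by restricted maximum likelihood with a Kenward-Roger approximation, and Data analysis names Stata 18.

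Under Sample size, the power calculation rests on a decaying structure: "Adjustment for time-varying correlations is made using a discrete time decay correlation structure". Its inputs are "assuming a within-period ICC of 0.03 and CV of 0.3", with the ICC varied from 0.005 to 0.05, and for the cluster autocorrelation, "Sensitivity of the CAC was explored using scores of 0.8 (0.6–0.9) in power calculations".

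**The concern.** A cluster intercept plus independent cluster-by-period effects produces only two correlations: one for two patients in the same cluster and period, and one lower value for two patients in the same cluster but different periods. Periods 1 and 2 are then as strongly correlated as periods 1 and 7. That is not decay with increasing separation.

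Two things are at stake. First, one statistician could follow the listed terms and another the decay sentence; they would fit different models and report different standard errors for the primary result. Second, the sponsor's own planning assumption is that correlation decays. If that is right, the listed model cannot represent it, and its standard error for the treatment effect is too small. Kenward-Roger adjusts both the degrees of freedom and the fixed-effect standard errors for small-sample uncertainty in the variance components, but it does not repair a wrong covariance form.

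**Working it through.** **Inputs from the protocol article.** Six clusters, one crossing over per period; enrolment in seven periods (Study design), although Sample size divides the sample over nine; 755 analysed at T3; SD 19, difference 8, two-sided alpha 0.05; ICC 0.03 (0.005–0.05); CAC 0.8 (0.6–0.9).

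**Layouts.** Seven periods: 755/42 = 18.0 per cluster-period. Nine periods: the article's 13 per cluster-period, or 755/54 = 14.0.

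**Assumptions.** Standard wedge, equal cells, fixed period effects, no covariates. Baseline FACT-B and location adjustment are left out because the article gives no figures for their effect.

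**1. Correlation by lag, at ICC 0.03 and CAC 0.8.**
- Nested exchangeable: ICC at lag 0, ICC × CAC at every other lag.
- Discrete time decay: ICC × CAC^lag.

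| Lag | 0 | 1 | 2 | 3 | 4 | 5 | 6 |
|---|---|---|---|---|---|---|---|
| Terms as listed | 0.030 | 0.024 | 0.024 | 0.024 | 0.024 | 0.024 | 0.024 |
| Discrete time decay | 0.030 | 0.024 | 0.0192 | 0.0154 | 0.0123 | 0.0098 | 0.0079 |

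**2. Power.** The covariance of a cluster's period means is V = SD² [R + I(1 − ICC)/m], with R from step 1 and m the cell size. The SE of the treatment effect comes from generalised least squares, and power = Φ(8/SE − 1.96).

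| Layout | Decay: SE, power | As listed: SE, power |
|---|---|---|
| 7 periods × 18 | 2.45, 90.5% | 2.33, 93.0% |
| 9 periods × 13 | 2.72, 83.6% | 2.57, 87.6% |

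The article's 90% is reproduced at base case by the decay structure with seven enrolment periods (89.8% after allowing for a cluster-size CV of 0.3). In both layouts the decay structure gives the lower power. At ICC 0.005 the two structures are practically the same (for example SE 2.020 and 2.016 at CAC 0.8, seven periods).

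**3. Type I error if decay is true and the listed model is fitted.** Take discrete time decay as the truth and find the cluster and cluster-by-period variances that restricted maximum likelihood settles on, with residual variance held at its true value. Compare the model-based SE with the true (sandwich) SE. Type I error = 2[1 − Φ(1.96 × SE_model/SE_true)].

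Base case, seven periods: SE_model 2.384, SE_true 2.473, ratio 0.964. Then 1.96 × 0.964 = 1.889, and the two-sided error is 5.9%.

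| ICC | CAC | 7 × 18: SE ratio, type I | 9 × 14: SE ratio, type I |
|---|---|---|---|
| 0.005 | 0.6 | 0.988, 5.3% | 0.987, 5.3% |
| 0.005 | 0.8 | 0.990, 5.2% | 0.988, 5.3% |
| 0.005 | 0.9 | 0.994, 5.2% | 0.992, 5.2% |
| 0.03 | 0.6 | 0.953, 6.2% | 0.942, 6.5% |
| 0.03 | 0.8 | 0.964, 5.9% | 0.950, 6.3% |
| 0.03 | 0.9 | 0.979, 5.5% | 0.968, 5.8% |
| 0.05 | 0.6 | 0.937, 6.6% | 0.920, 7.1% |
| 0.05 | 0.8 | 0.953, 6.2% | 0.930, 6.8% |
| 0.05 | 0.9 | 0.973, 5.6% | 0.955, 6.1% |

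These figures use a normal reference and include no Kenward-Roger adjustment.

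**The case against.** The strongest reply is that the article never says the cluster-by-period effects are independent. Read with the decay sentence and the power section, the intended model may have autoregressive effects, with the covariance type left to an analysis plan that is not shown. Part of this stands: the intention may be sound, and one added clause could settle it. But the article lists the terms and credits them with a property that, in their ordinary form, they lack. An unseen plan does not make that statement correct.

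Three stronger readings are tempting, and the documents do not support them.

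- *The trial is underpowered because the structures differ.* The reverse holds at base case: planning used the structure with the lower power. Fitting the listed model when decay is true costs little precision (true SE 2.47 against 2.45). The lower power of the nine-period layout is a separate matter of periods and cell size.
- *A cluster intercept with autoregressive cluster-by-period effects would also be wrong.* Its correlation falls to a floor, so it is not identical to the planning structure. But it contains discrete time decay as the special case of zero intercept variance, so it is more general and not misspecified under decay. Dropping the intercept is a preference for matching the power calculation, not a requirement.
- *The primary test is seriously invalid.* The treatment estimate stays unbiased, the base-case excess is about 0.9 percentage points, and at the lowest documented ICC it is 0.2–0.3 points.

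**Conclusion.** The point holds. The statement about the primary model is wrong for the terms as listed and disagrees with the Sample size section. The consequence is moderate and anti-conservative. With seven enrolment periods the standard error is about 1–6% too small, and type I error is about 5.2–6.6% over ICC 0.005–0.05 and CAC 0.6–0.9. With nine periods, type I error reaches about 7.1% at the unfavourable end (ICC 0.05, CAC 0.6).

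This rests on two conditions: the cluster-by-period effects are fitted as independent, and correlation really decays, as the sponsor assumed for planning. The exact rate under the planned Kenward-Roger test was not computed. The design is not overturned, but the choice of structure should be settled before the outcome data are analysed.

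**What to change.** Choose one structure before analysis and say so in both sections.

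- **Option A, matching the power calculation.** State that the cluster-by-period effects have an AR(1) (discrete time decay) covariance within cluster, with correlation r^|s−t| between periods s and t, preferably without a separate cluster intercept. Name software confirmed to fit this with a small-sample correction, and amend the Stata statement if needed. Pre-specify nested exchangeable as the fallback on non-convergence and as a sensitivity analysis.
- **Option B, keeping the listed terms.** State that the effects are independent, delete the decay sentence, restate power under nested exchangeable, and add the decay model as a sensitivity analysis.

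The cost is wording and, for Option A, possibly different software for one model and a small convergence risk with six clusters, which the named fallback covers. Option B leaves the inflation above in place if decay is real; the sensitivity analysis would then show whether the conclusion depends on it.
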